# RECRUITMENT AND RETENTION OF SUBJECTS

***Recruitment/Consent/Stratification:*** Sharp Mary Birch Hospital for Women & Newborns and the Neonatal Research Institute (NRI) has an in-house parent advisory group that reviews trial designs to determine how parents may feel about them and whether the consent is clear and appropriate. A waiver for delayed consent is proposed in order to successfully complete the trial with minimal selection bias in a reasonable period of time. The research presents no more than minimal risk of harm to subjects. There are no known long term consequences of having leads applied to the surface of the skin. We now have compelling evidence that trials which require consent before delivery are likely to enroll a population that is not as sick as those eligible but not enrolled, which would decrease the generalizability of this large important trial. Rich et al. (Pediatrics 2010, 126: e215-e221) found that infants who were approached for participation in SUPPORT were significantly different from non-approached infants who were eligible for this trial and were born in the recruiting centers. Enrolled infants were more likely to be white, have mothers with better education and health insurance, and have prenatal care. They were less likely to be in the most immature gestational age week for this study. Antenatal Consent has been shown to limit the enrollment of the sickest infants in studies by eliminating the ability to obtain consent from

mothers with limited prenatal care and/or emergent deliveries. We believe that the use of antenatal consent would adversely affect the generalizability of the data obtained. A member of the research team will approach the parents after delivery to discuss the study. A delayed informed consent will be obtained to use the infant's data in the study and obtain neurodevelopmental follow up data.

Therefore pregnant women at <32 weeks gestation dated by their earliest ultrasound or last menstrual period will be approached for consent. In the past 12 months, the Sharp Mary Birch obstetric service had 150 premature newborns delivered by C/S. The demographics of our population are about 40 percent Caucasian, 30 percent Hispanic, 15 percent Asian Pacific

Islander, 7 percent African American and 8 percent other (Native American, etc.).

Inclusion and exclusion criteria are shown in **Table 1.**

| **Table 1** | **INCLUSION**  **Criteria** | **EXCLUSION**  **Criteria** | **REASON** |
| --- | --- | --- | --- |
| Gestational Age | 23 to 31+6 weeks |  | This GA most likely to require resuscitation interventions. Delayed consent will be obtained to allow for urgent unplanned deliveries to be included in the trial such as emergency C-Section, etc. |
| Parental refusal to participate |  | X | Parents may refuse participation antenatally or after delivery. |
| Congenital Anomalies |  | X | Increased risk for poor long-term outcomes and death. |
| Moderate to severe head bruising upon delivery |  | X | Difficulty in assessing skin integrity with dark bruising |

***Study Protocol:*** Currently, all infants taken to the resuscitation suite have recordings of heart rate, oxygenation, and airway pressure, along with simultaneous video recording. These recordings are reviewed monthly as part of our quality improvement process. Routine use of EEG or NIRS monitoring may be used per physician preference. Therefore the only additional component of the study will be the placement of electrodes (EEG) and a single sensor (NIRS) at the time of birth. ECG will be available in half of the infants per randomization during resuscitation. Upon identification of an eligible delivery, an additional research coordinator will be on standby to assist with placement of sensors.

EEG electrodes, NIRS probes, ECG electrodes and pulse oximetry will be applied within 60 seconds of the newborn being placed on the warmer. We piloted this procedure in four recent emergency C/S deliveries in which the research team successfully applied adhesive sensors within 60 seconds without interfering with resuscitation. The average time to display EEG and NIRS signals were 32 and 63 seconds, respectively. The placement of the sensors and tracing from one example are shown in **Figure 3**. (*Note – Removed for inclusion of protocol in publication*) While saturation and heart rate data will be available to the clinical team, data from both aEEG and NIRS will be blinded.

Additional monitoring will begin once the newborn is in the NICU. Electrical Cardiometry sensors (which can measure cardiac output and stroke volume) using four EC sensors (Electrical Cardiometry, Cardiotronic, La Jolla, CA) will be placed on the newborn’s chest.

Cerebral StO2, cardiac output, and stroke volume will be recorded every two seconds and linked with other variables that will be downloaded from the infant’s hospital bedside monitor.

These will include blood pressure, heart rate, and blood oxygen levels. In addition, physical exams as well as gathering the continuous bedside physiological data can be accumulated in a blinded fashion and the data will be submitted to the statistician (DG), who will remain blinded to the intervention for the duration of the study. Following study enrollment, data will be collected from the mothers and the newborns. Research data is shown in **Table 2**.

**Table 2: DATA COLLECTED FROM NEWBORNS AND MOTHERS**

**Clinical Data collected from all enrolled mothers:**

1. Age
2. Education Level
3. Insurance (private/public)
4. Primiparous (yes/no)
5. Ethnicity
6. Chorioamnionitis (yes/no)
7. Pre-Eclampsia (yes/no)
8. Duration of rupture of membranes.
9. Antenatal Steroids (yes/no)
10. Antenatal Magnesium (yes/no)
11. Cesarean Section (yes/no)
12. Reason for Cesarean Section
13. Placental Weight (grams)

**Clinical Data collected from all enrolled infants:**

1. Gestational Age
2. Gender
3. Weight (grams), length (cm) and head circumference (cm)
4. Diagnoses
5. APGARS at 1 and 5 minutes
6. Cord Gases (pH, Base deficit, arterial and venous)

**Measured Endpoints and Recorded Outcomes**

1. Amplitude Integrated EEG signal over the first 10 minutes of life
2. Cerebral StO2 by Near-InfraRed Spectroscopy within the first 10 minutes of life
3. Resuscitation (yes/no)
4. Resuscitation score (1-6)
5. DR Interventions: PPV, CPAP, intubation, chest compressions, volume, medications (yes/no)
6. Maximum inspired oxygen (FiO2) (percentage)
7. Maximum Peak Inspiratory Pressure (cm H20)
8. Time to reach heart rate 100 beats per minute (seconds)
9. Mean Blood Pressure (by non-invasive oscillimetry) at 10 minutes
10. Cardiac Output by Electrical Cardiometry (ml/kg/min) for 72 hours
11. Cerebral StO2 by Near-Infrared Spectroscopy for 72 hours
12. EEG pattern: normal- suppressed, seizure activity for 72 hours
13. Mean Arterial Blood Pressure (mm Hg)
14. Use of cardiac inotropes (dopamine, dobutamine, epinephrine) (yes/no)
15. Presence of brain injury on MRI (yes/no) (if clinically indicated)

Our engineering collaborators will help synchronize EEG and NIRS onto the existing video-analog monitoring setup to simultaneously collect information on heart rate, body oxygenation, oxygen usage by the brain, and electrical activity of the brain. We will gather their

inpatient data to look for adverse events of premature birth and resuscitation (i.e., brain bleeding, anoxic brain injury, death) and will incorporate this data with our evaluation of the neurological and physiological data gathered during the resuscitation. Additionally, all enrolled infants will have a detailed brain ultrasound within 24 hours of birth and again at one week. An MRI will be performed when they reach full-term equivalence if clinically indicated as standard of care. The brain ultrasounds will alert us to any brain bleeding, and the MRI will reveal the full extent of any brain injury of prematurity. Given the known association between extensive resuscitation with brain bleeding and death, more evidence is needed about the physiologic responses of the brain and the body during resuscitation so that resuscitation practices can be improved to promote healthy brain development and to avoid potentially devastating outcomes.

# Description of evaluation measures to assess project results and outcomes.

Our overall aim for this project is to provide preliminary data about the premature brain during the birth transition and resuscitation. Increased understanding of how the premature brain responds during this critical time will provide a physiological basis of improving the resuscitation process, will demonstrate the feasibility of such monitoring, and will be used to determine optimal practice for these vulnerable infants and improve their quality of life. After the successful conclusion of this project, we will apply specific interventions at birth in the preterm population and evaluate the resultant effects on neuro-monitoring. This will be in the context of a large randomized controlled trial powered to demonstrate improvements in long-term neurodevelopmental outcomes in children.

Given the known association between extensive resuscitation and outcomes such as bleeding in the brain and death, we expect to find physiological changes in newborns

immediately after birth and during the first 72 hours of life. We expect to find very early, potentially correctable changes in physiology that may be able to protect the brain before injury can take place.

We will also collect routine follow-up visit information at 18–30 months corrected gestational age to see if there is any correlation between NIRS and aEEG during the first 3 days of life to long term neurodevelopmental outcomes.

**STATISTICAL CONSIDERATIONS (Sample Size and Power Calculation):** All aspects of data

analysis and statistical investigations will be directed by [name], who has formal training in Statistics and has expertise in multivariate datasets such as these.

**Statistical Analysis**: To test the primary efficacy endpoint a 2 x 2 chi-square test will be

conducted at each one minute interval, and the attendant effect size for the 2 x 2 contingency analyses (i.e., phi) will be reported. As well, relative risk (RR) and odds ratio (OR) statistics will be reported (along with 95 percent confidence intervals). For interval-level, continuous outcomes one-way ANOVA will be conducted and all assumptions will be tested/examined (normality, homogeneity of variance, etc.). Nonparametric options (e.g., Mann-Whitney) will be considered in case remedial measures such as transformations do not meet the parametric assumptions. We will compare continuous data measures averaged over each MOL using multi- variate linear regression analysis. We will use linear, logistic or generalized linear models to evaluate demographic variables and clinical outcome variables all using SPSS vs. 22.0 or Stata 11.0.

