# The Neu-Prem Trial: Neuromonitoring of Preterm Newborn Brain During Birth Resuscitation

**Principal Investigator**: [name]

**Co-Investigators:** [name],

**Consultant:** [name]

**Length of Study**: 2 years

# Number of subjects to be studied: 130

**Age range of subjects**: Premature newborns between 23 to 32 weeks gestation

PROPOSAL NARRATIVE.

**Goals, hypothesis and objectives.** The goal for this trial is to characterize the normal brain function of 130 very premature newborns (23 to 32 weeks gestation) during the first 72 hours of life. This is the first observational study to evaluate brain perfusion and function in 130 premature newborns ***starting at the time of birth.***

Our primary hypothesis is that simultaneously recording physiological changes of the newborn (brain activity, brain oxygenation, blood pressure, blood oxygenation, cardiac function and heart rate) beginning at birth will help us predict which babies will develop adverse problems such as bleeding in the brain (intraventricular hemorrhage, IVH) and its resultant neurological problems. We hypothesize that newborns **with low brain perfusion** and **low brain activity** at birth will have **poor outcomes** such as bleeding in the brain and death. We will measure these components of brain function using two sophisticated, non-invasive technologies. First, amplitude integrated electroencephalography (aEEG), a “simplified” EEG with four sensors (single channel), enables continuous non-invasive monitoring of cerebral activity. Second, near-infrared spectroscopy (NIRS) provided by FORE-SIGHT Elite Absolute Tissue Oximeter, is another non-invasive technology that allows continuous real-time measurement of regional tissue oxygen utilization of the brain. Both technologies are FDA approved in newborns and have been predictive of brain injury or neurodevelopmental impairment. [1-9]

Our proposal builds on an ongoing research program at a nationally recognized level 3 center with the largest number of births in California. With several completed and ongoing trials in preterm infants, our group is uniquely positioned to lead this clinical trial. (ClinicalTrials.gov:

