# Size of the population to be studied in terms of age, gender, ethnicity, the source of subjects and the recruitment process.

In 2014 more than 9,400 babies were born at Sharp Mary Birch Hospital for Women and Newborns, and 1,500 babies were admitted into the NICU. In our most recently completed trial in premature infants with identical eligibility criteria (23-32 weeks gestation), we recruited 150 subjects in less than 2 years. (Platform Presentation: Katheria et al, E-PAS 2015). Therefore, we are confident that we will be able to enroll the 130 newborns needed over the two year grant period. This figure is also conservative to include a parental refusal rate of 20 percent since we do not anticipate many parents would refuse to participate given the minimal risks of the study. Every premature newborn from 23 to 32 weeks gestation born at Sharp Mary Birch will be considered for enrollment until we reach our target of 130 newborns over the two year period.

**Study Timeline:** We anticipate it will take 18 months to recruit 130 infants and six months to

collect and analyze data for publication and presentation at a national meeting (total 24 months). We do not anticipate that any subjects would drop out since the intervention is performed at birth.

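### The stated two-year study length cannot accommodate the follow-up at 18 to 30 months corrected age that the protocol also plans

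*Protocol*

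**What the plan says.** The front matter of the Protocol states "Length of Study: 2 years". The Study Timeline paragraph, in the section on the size of the population, breaks this down. Recruiting the 130 infants is given 18 months, and the use of the remaining six, with the sum, is described as follows: "collect and analyze data for publication and presentation at a national meeting (total 24 months". The same paragraph expects no drop-out, because the intervention takes place at birth. The section on acknowledging Foundation support promises meeting presentations within two years of study start.

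The section describing evaluation measures adds a later data collection: "We will also collect routine follow-up visit information at 18–30 months corrected gestational age". Its purpose is to look for a "correlation between NIRS and aEEG during the first 3 days of life to long term neurodevelopmental outcomes". Under Recruitment and Retention of Subjects, consent for this is foreseen: "A delayed informed consent will be obtained to use the infant's data in the study and obtain neurodevelopmental follow up data". Table 1 sets gestational age at birth at "23 to 31+6 weeks".

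The Protocol describes no study phase, data collection or report after month 24, and gives no expected number of infants with follow-up.

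**The concern.** Recruitment period, total length and follow-up window are all fixed in the Protocol, and they cannot all hold. An infant enrolled at the end of recruitment is six months old when the study is said to end, and the planned assessment lies more than a year beyond that.

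The exploratory neurodevelopmental correlation is what is at stake. If the study closed at month 24 with that aim still in place, the only usable infants would be those born in the first few months of enrolment, all near the young end of the visit window. A reader who takes the study duration from the front matter would also be given a figure well short of what the follow-up needs. The expectation of no drop-out has the same weakness: its reason covers the birth intervention, not routine visits roughly two years later.

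**Working it through.** **Inputs from the Protocol**
- Recruitment: 130 infants in 18 months (Study Timeline).
- Total length: 24 months (front matter, Study Timeline).
- Gestational age at birth: 23+0 to 31+6 weeks (Table 1).
- Follow-up window: 18 to 30 months corrected age (evaluation measures).

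**Assumptions not in the Protocol**
- Uniform accrual.
- Corrected age is chronological age minus the time from birth to 40 weeks.
- One month is 30.44 days.

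**The plan's own figure.** 18 + 6 = 24 months. It reproduces.

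**Step 1: age correction** = (280 days − gestational age in days) / 30.44
- 23+0 weeks (161 days): 119 / 30.44 = 3.91 months
- 31+6 weeks (223 days): 57 / 30.44 = 1.87 months

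**Step 2: time from birth to 18 months corrected**
- 23+0: 18 + 3.91 = 21.91 months
- 31+6: 18 + 1.87 = 19.87 months

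**Step 3: infants who can be 18 months corrected by month 24.** The accrual rate is 130 / 18 = 7.22 per month, and an infant qualifies only if enrolled in the first (24 − age needed) months.

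| Gestational age | Enrolled within first | Infants | Share of 130 |
|---|---|---|---|
| all 23+0 | 24 − 21.91 = 2.09 months | 2.09 × 7.22 = 15.1 | 11.6% |
| all 31+6 | 24 − 19.87 = 4.13 months | 4.13 × 7.22 = 29.8 | 22.9% |
| evenly spread | mean of the two, 3.11 months | 3.11 × 7.22 = 22.5 | 17.3% |

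These are upper bounds. They ignore deaths, missed visits and the time needed for analysis before month 24.

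**Step 4: upper end of the window.** This needs no accrual assumption. An infant enrolled on the first day is at most 24 − 3.91 = 20.1 (23+0) to 24 − 1.87 = 22.1 (31+6) months corrected at month 24. None can be 30 months corrected.

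**Step 5: when the last infant, enrolled at month 18, gets there**
- 18 months corrected: 18 + 19.87 = 37.9 to 18 + 21.91 = 39.9
- 30 months corrected: 12 months later, 49.9 to 51.9

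Against 24 months, the shortfall is 37.9 − 24 = 13.9 months at the least and 51.9 − 24 = 27.9 months at the most.

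**Sensitivity of the count at month 24**
- Accrual over 24 months, which the wording "will be considered for enrollment until we reach our target of 130 newborns over the two year period" would allow: 130 × 2.09 / 24 = 11.3 to 130 × 4.13 / 24 = 22.4.
- Accrual over 12 months: 130 × 2.09 / 12 = 22.6 to 130 × 4.13 / 12 = 44.7.
- No correction for prematurity, 18-month accrual: 130 × 6 / 18 = 43.3.

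In none of these cases do more than about a third of the infants reach the start of the window.

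**The case against.** The strongest reply is that the 24 months are a funding and first-report timeline. The section on the size of the population calls them a grant period, the six months after recruitment lead to a meeting presentation, and the follow-up is introduced separately and uses routine visits. No sentence says that follow-up stops, or that the correlation is analysed, at month 24. This is a plausible account of what was intended. It does not remove the inconsistency, because the front matter presents two years as the length of the study and no later phase is described anywhere.

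The reply does limit the consequences. A reader might infer that the neurodevelopmental analysis will either never happen or be run on the first 12% to 23% of infants. The Protocol does not support that: routine records can be retrieved and reported after the main paper, and no early neurodevelopmental analysis is planned.

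A reader might also infer a gap in consent. The Protocol says that the delayed consent extends to neurodevelopmental follow-up data, and the consent pages are not available for checking, so no gap can be shown.

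Two further points stand. The count of 15 to 30 depends on uniform accrual, and each end puts every infant at a single gestational age. The aim is exploratory and absent from the list of measured endpoints and recorded outcomes in Table 2. Formal data locks would ordinarily be left to the analysis plan, so none is asked for here.

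**Conclusion.** The point holds as an internal contradiction about study length. A 24-month study with 18 months of recruitment cannot contain follow-up at 18 to 30 months corrected age. On uniform accrual, at most about 15 to 30 of 130 infants, about 22 with evenly spread gestational ages, could reach the start of the window by month 24. The exact count moves with the accrual pattern; the conclusion does not. That no infant can reach 30 months corrected by month 24, and that the last infant enrolled at month 18 is not 18 months corrected until about month 38 to 40, follows from the Protocol's own figures and the usual definition of corrected age.

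The weight is moderate. One exploratory aim and the stated duration are affected. The randomised ECG comparison, the primary analysis and all in-hospital outcomes are not.

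**What to change.** 1. State that the 24-month timeline covers recruitment and the in-hospital (neonatal) report only.
2. Restate the total study length. If one visit at or after 18 months corrected is used, about 40 months is the earliest point by which every infant has reached that age. If visits anywhere in the window count, about 52 months is needed. Add analysis time in either case. Both figures assume that recruitment ends at month 18. If it ran for the full two years, each would be six months later (about 46 and 58).
3. Say that the exploratory correlation of NIRS and aEEG with neurodevelopment is run only after that follow-up is complete.
4. Limit the expectation of no drop-out to the neonatal phase.

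The cost is a few sentences in the Protocol, a longer stated duration and later chart retrieval. The visits are already routine, so none is added.

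### The primary endpoint is tested by a separate chi-square at each minute, and the protocol names no decisive minute, overall test or multiplicity adjustment

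*Protocol*

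**What the plan says.** The Statistical Analysis paragraph, in the protocol section on evaluation measures, opens with the primary test: "To test the primary efficacy endpoint a 2 x 2 chi-square test will be" and continues "conducted at each one minute interval, and the attendant effect size for the 2 x 2 contingency analyses (i.e., phi) will be reported". Relative risks and odds ratios are to be reported as well, "along with 95 percent confidence intervals". For continuous data the same paragraph says: "We will compare continuous data measures averaged over each MOL", using regression.

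The paragraph does not say which listed outcome is the primary efficacy endpoint, which two groups form the table, how many one-minute intervals there are, or what significance level applies. The nearest indication of a window is in the list of measured endpoints, whose first two items are "Amplitude Integrated EEG signal over the first 10 minutes of life" and "Cerebral StO2 by Near-InfraRed Spectroscopy within the first 10 minutes of life". Neither is labelled primary. The title page gives "Number of subjects to be studied: 130", and the Study Protocol text makes ECG available to a randomised half of the infants.

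**The concern.** A primary analysis should give one answer at a known error rate. Here the protocol specifies one test per minute and no way to turn the set into a single conclusion. If minute 4 is significant and the others are not, nothing in the protocol says whether the primary result is positive. Anyone following the text could report whichever minute crossed the threshold, and with several chances to cross it, the error rate for the series exceeds that of a single test. Separate confidence intervals for each minute's relative risk and odds ratio carry the same problem in interval form.

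This goes beyond detail that a protocol may leave open. The protocol has already chosen a minute-by-minute primary test, and a later plan that named one minute or one model would be changing that choice.

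**Working it through.** **The plan's own figure.** There is none to reproduce. The heading announces a sample size and power calculation, but no alpha, power, effect size or event rate follows. The only design figure is the total of 130.

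**Inputs**
- Number of tests k: not stated. Assumed 10, from the 10-minute window of the first two listed endpoints; 5 is shown as a smaller case.
- Level per test: not stated. Assumed two-sided 0.05; the only support is the 95% confidence level.
- Groups: not stated for this test. Assumed to be the ECG randomisation, 130 / 2 = 65 per arm.
- Decision rule: not stated. Assumed that any significant minute counts as positive.
- Correlation between minutes: not stated. Readings repeat on the same infant, so it should be positive; varied from 0 to 0.95.

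**Independent minutes.** The chance of at least one false positive is 1 - (1 - 0.05)^k.
- k = 10: 1 - 0.95^10 = 0.401
- k = 5: 1 - 0.95^5 = 0.226

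**Correlated minutes, simulated trials.** 65 against 65 infants with no group difference, ten chi-square tests without continuity correction, and binary data cut from correlated normal variables at prevalence 0.5 and 0.2. There were 6,000 trials per setting. Each cell gives the proportion of trials with at least one significant minute at the two prevalences.

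| Latent correlation | Adjacent-minute (AR(1)) | Equal between all minutes |
|---|---|---|
| 0 | 0.368, 0.393 | 0.362, 0.394 |
| 0.7 | 0.316, 0.356 | 0.268, 0.288 |
| 0.8 | 0.287, 0.324 | 0.233, 0.264 |
| 0.9 | 0.245, 0.271 | 0.192, 0.212 |
| 0.95 | 0.202, 0.239 | 0.157, 0.178 |

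For correlations of 0.7-0.95 this is about 16-35%. With k = 5 the same simulation gives about 12-21% over those correlations.

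**Continuity correction.** The protocol does not say whether it will be used. It makes each test conservative. Ten tests then give about 26% at independence and about 10-24% for latent correlations of 0.7-0.95.

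**Correlation placed directly on the test statistics.** Dichotomising weakens correlation, so this is a stronger dependence than the same number in the table. With 400,000 draws and k = 10, correlation 0.7 gives 0.300 (AR(1)) or 0.214 (equal), 0.9 gives 0.188 or 0.127, and 0.95 gives 0.140 or 0.100.

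**Effect of a simple adjustment.** Bonferroni with k = 10 uses 0.05 / 10 = 0.005 per minute, and 1 - 0.995^10 = 0.049 if the minutes are independent. In the 65-per-arm simulation it held the rate to about 2.5-5.6%.

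**The case against.** **The study is exploratory.** The protocol calls itself observational, says that its overall aim is preliminary data, and plans a later powered trial. That lowers the stakes but does not remove the point. The same protocol names a primary efficacy endpoint, randomises ECG availability, and expects its findings to inform practice and national guidelines.

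**A statistical analysis plan may contain the adjustment.** This stands as far as it goes: one can say only that the protocol states none. A reader might infer that the trial has no defined type I error at all, and the protocol alone cannot show that.

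**The size is assumption-driven.** This stands. A reader might take 22-40% as the actual error rate. However, 40% needs independent minutes and an uncorrected test, and 22% is not a floor. Stronger or equal correlation, or a continuity correction, takes the rate for ten tests down to about 10%. The 65 v 65 split is also assumed: the primary hypothesis concerns low brain perfusion and activity predicting bleeding and death, so the table might compare other, unequal groups.

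**Three further inferences are not supported.**
- Because the pilot reports "The average time to display EEG and NIRS signals were 32 and 63 seconds, respectively", one might conclude that the minute-1 test would lack data. That presumes a NIRS-based primary endpoint, which the protocol does not name, and rests on an average from four deliveries.
- Counting 20 tests, for a rate of 1 - 0.95^20 = 64%, presumes that both brain signals are primary.
- Standard errors would be too small if minutes were pooled as independent rows, but the regression sentence does not say that they will be.

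**Conclusion.** The concern holds in a limited form. The protocol fixes its primary test as a repeated one and gives no decisive minute, overall test or adjustment. Under the four assumptions listed (ten minutes, two-sided 0.05 per test, 65 v 65 by ECG randomisation, any minute counts), the false-positive rate is up to about 40% with independent minutes. It is roughly 10-35% under strong within-infant correlation. Every ten-minute case examined is at least double the assumed 5%.

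The absence of error control in the protocol's stated primary test is read directly from the text. The percentages are illustrations, because the protocol supplies neither the number of intervals, nor the level, nor the groups, nor the decision rule. The need for the change does not depend on where in the range the true figure lies.

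**What to change.** Replace the opening sentence of the Statistical Analysis paragraph with one that names the primary endpoint, the groups compared and a single primary test at two-sided 0.05. Any of these would do:
- one overall group effect from a repeated-measures model with infant as the cluster (GEE with a logistic link if the endpoint is binary, a linear mixed model if it is continuous);
- one pre-specified minute;
- one summary measure over the window.

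Keep the per-minute phi, relative risk and odds ratio with confidence intervals as descriptive results without significance claims, or adjust them by Holm's method.

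The cost is one paragraph of wording, with no new data and no change to the sample size of 130. The downside is that an isolated significant minute can no longer be claimed as a primary result.

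### The only test and effect measures named for the primary endpoint are unadjusted, and no analysis commits to gestational age, so immaturity could pass for a brain-monitoring effect

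*Protocol*

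**What the plan says.** Under Goals, hypothesis and objectives, the protocol's primary hypothesis is that recording physiology from birth "will help us predict which babies will develop adverse problems such as bleeding in the brain". It expects infants with low brain perfusion and low brain activity to have the poor outcomes, namely brain bleeding (IVH) and death.

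The Statistical Analysis paragraph then fixes the following:

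- The main test is introduced with the words "To test the primary efficacy endpoint a 2 x 2 chi-square test will be"; its stated timing is "conducted at each one minute interval", and phi is the effect size. The endpoint is called an efficacy endpoint but is not named, and the rows and columns of the table are not given.
- On further effect measures for that test, it adds that "relative risk (RR) and odds ratio (OR) statistics will be reported (along with 95 percent confidence intervals".
- On readings taken minute by minute, it says "We will compare continuous data measures averaged over each MOL using multi- variate linear regression analysis".
- A separate sentence covers other variables, again without naming any covariate: "We will use linear, logistic or generalized linear models to evaluate demographic variables and clinical outcome variables".

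Table 1 sets eligibility at "23 to 31+6 weeks". The first item in the list of infant data is "Gestational Age". No analysis in the protocol names it as a covariate or stratum. The recruitment section has the word stratification in its heading, but its text describes none.

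**The concern.** The cohort spans nine completed weeks of gestation (23 to 31). Gestational age may well influence both the predictors (cerebral StO2, aEEG) and the outcomes (IVH, death). If it does, a crude RR or OR mixes what the monitor shows with what was known before any sensor was applied.

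This matters because of how the results are to be used. The section on evaluation measures expects to find early changes that might be corrected to protect the brain. The section on expected impact wants evidence that monitoring is predictive, in support of national guidelines. The first use needs an association that is not just immaturity. The second needs evidence that the monitor adds to gestational age. A crude 2 x 2 table supplies neither.

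**Working it through.** **There is no plan figure to reproduce.** The protocol states 130 infants but gives no alpha, power, effect size, event rate, share of infants with low StO2 or aEEG, or relation of either to gestational age. Everything below except N = 130 and the age range is an assumption, and shows mechanism and range only.

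**Step 1: two age strata, no monitor effect within either.** For stratum s let w be its share of infants, l the fraction with a low reading and e the fraction with IVH or death, with l and e independent within the stratum. The collapsed table is

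- a = Σ w·l·e (low, event)
- b = Σ w·l·(1−e) (low, no event)
- c = Σ w·(1−l)·e (not low, event)
- d = Σ w·(1−l)·(1−e) (not low, no event)

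with RR = [a/(a+b)] / [c/(c+d)] and OR = ad/(bc). The rejection rate is that of a noncentral chi-square (1 df) with noncentrality 130·phi², at two-sided 0.05.

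Worked case, with 30% of infants in the younger stratum, low reading in 30% (younger) v 10% (older), events in 40% v 10%:

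- a = 0.3·0.3·0.4 + 0.7·0.1·0.1 = 0.043
- b = 0.3·0.3·0.6 + 0.7·0.1·0.9 = 0.117
- c = 0.3·0.7·0.4 + 0.7·0.9·0.1 = 0.147
- d = 0.3·0.7·0.6 + 0.7·0.9·0.9 = 0.693
- RR = (0.043/0.160)/(0.147/0.840) = 1.54
- OR = (0.043·0.693)/(0.117·0.147) = 1.73
- phi = 0.088, rejection rate 17%

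| Younger share | Low reading, younger v older | Events, younger v older | Crude RR | Crude OR | Rejection |
|---|---|---|---|---|---|
| 30% or 40% | 25% v 25% | 30%, 40% or 50% v 10% | 1.00 | 1.00 | 5% |
| 40% | 20% v 10% | 30% v 10% | 1.23 | 1.29 | 7% |
| 30% | 30% v 10% | 40% v 10% | 1.54 | 1.73 | 17% |
| 40% | 50% v 20% | 40% v 10% | 1.53 | 1.74 | 25% |
| 40% | 50% v 10% | 50% v 10% | 1.96 | 2.62 | 62% |

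The true RR within each stratum is 1 in every row. The first row shows that the bias vanishes if the reading does not vary with gestational age.

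**Step 2: continuous gestational age, crude against adjusted.** In 2,000 simulated trials of 130 infants, gestational age was uniform over 23 to 32 weeks. The low-reading probability fell from about 63% at 23 weeks to 7% at 31.9 weeks, and the event probability from about 51% to 4%. There was no monitor effect. The crude chi-square rejected in about 32% of trials (crude RR about 1.6). Logistic regression adding gestational age rejected in about 5.6% (adjusted OR about 0.97). The Monte Carlo standard error of that last rate is √(0.0555·0.9445/2000) ≈ 0.5 percentage points, so it is compatible with 5%.

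**Step 3: varying the correlation r between reading and gestational age.** Event risk was 35-50% at 23 weeks, falling to 8-10% at 31 weeks, and the low group was 10%, 25% or 50% of infants. Over two runs, crude rejection was about 6-13% for r = 0.2-0.3, 10-30% for r = 0.4-0.5 and 16-53% for r = 0.6-0.7. With gestational age in the model, checked only for r = 0.2-0.5, rejection was about 4-8%.

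**The case against.** **The table may not be the one at issue.** A reader might infer that the protocol commits to reporting the StO2/aEEG link with IVH or death as a crude chi-square, RR and OR. It does not say so. The endpoint is unnamed, the word efficacy suits a randomised comparison, and the only two-group contrast the protocol defines is ECG available or not. In that contrast gestational age is not a systematic confounder and crude measures are ordinary practice. This stands, and it makes the point conditional. It does not remove it: on the ECG reading, the primary hypothesis is left with no specified adjusted analysis at all.

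**Adjusted modelling is foreseen.** A reader might also infer that regression is excluded. It is not: the last two analysis sentences plan linear, logistic and generalised linear models, and gestational age could enter them. But neither sentence makes StO2 or aEEG the predictor of IVH or death, and neither names gestational age. They permit the adjustment without committing to it.

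**Covariate lists belong in a statistical analysis plan.** Often true, and one may exist. But the protocol is not silent here: it names specific unadjusted measures for the primary endpoint. That is the choice being questioned.

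**Prediction does not need adjustment.** For prediction alone a crude association is not wrong. The useful question is still what the monitor adds to gestational age, and the wish to read changes as correctable goes beyond prediction.

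**A low cut-off pooled over all weeks.** It is tempting to add that such a cut-off would make the low group largely the immature group. The protocol sets no cut-off. The tenth-percentile figure it mentions describes a normative range in a cited study. That criticism is not supported.

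**Conclusion.** The point holds in conditional form. What the documents establish is that the only test and effect measures specified for the primary endpoint are unadjusted, that the cohort runs from 23 to 31+6 weeks, that gestational age is collected, and that no analysis commits to using it. If those measures serve the primary hypothesis, immaturity can appear as a monitoring effect.

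The size cannot be derived from the protocol. Under assumed inputs with no true monitor effect, crude rejection runs from about 5% with no relation between reading and gestational age to about 30-50% with a strong one. The extreme two-stratum setting gives 62%. Adjusted rejection was about 4-8%, but this was not checked at r = 0.6-0.7, where the largest of the step 3 crude rates arise. At r = 0.2-0.3 the crude and adjusted ranges overlap. The figures do not show that the trial's result will be spurious; they show that a crude result could not be told apart from a gestational-age effect.

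**What to change.** In the Statistical Analysis paragraph:

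1. Name the primary endpoint and give the rows and columns of the 2 x 2 table, so that it is clear whether it is the ECG contrast or the monitoring association.
2. State that the association of StO2 and aEEG with IVH or death is estimated primarily by logistic regression with gestational age (continuous, in weeks and days) always in the model.
3. Report the gain from StO2 and aEEG over a model with gestational age alone, for example by a likelihood-ratio test and the change in discrimination.
4. Keep crude RR and OR for this association as descriptive.

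The cost is a few sentences; the covariate is already collected. The interval will be slightly wider and the effect estimate probably smaller than the crude one. Events may be few. With the roughly 22-25 events assumed in the step 3 simulation and three coefficients (StO2, aEEG, gestational age), there are about 22/3 ≈ 7 to 25/3 ≈ 8 events per coefficient. The model should therefore stay this small, and a penalised likelihood would be a sensible safeguard.
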